## Abstract

**Introduction:**

Cervicogenic headache (CEH) is a secondary headache characterized by chronic, unilateral headache. Ultrasound-guided injections of the greater occipital nerve (GON) and the third occipital nerve (TON) are effective in the treatment of CEH, as is meridian sinew tuina for the treatment of CEH, but the evidence of clinical efficacy of combining these two therapies is valid. Therefore, we have designed a randomized controlled trial with the aim of investigating the efficacy and safety of ultrasound localization meridian sinew tuina combined with GON and TON injections for the treatment of CEH.

**Methods and analysis:**

In this study, we enroll 60 patients experiencing CEH. The control group receives ultrasound-guided injections of GON and TON. The intervention group is treated with ultrasound localization meridian sinew tuina combined with the injection of GON and TON. Meridian sinew tuina is performed once a day for 30 min for 3 days. The primary observational index includes the Short-Form of McGill Pain Questionnaire (SF-MPQ). The Secondary outcomes include Cervical Range of Motion (ROM) and Medical Infrared Thermography (MIT). MIT is used to measure the change in skin temperature in the area of the patient’s meridian sinew tuina treatment of GON and TON before and after the intervention. There are 5 time points assessed as baseline, day 3, day 15, day 30, and day 60.

**Discussion:**

This study proposes to combine ultrasound-guided injections of GON and TON for the treatment of CEH after identifying the treatment area of meridian sinew tuina under ultrasound localization. Meanwhile, MIT is utilized to provide objective evidence of the efficacy of CEH.

**Clinical trial registration:**

ChiCTR2300076128.

## Introduction

Cervicogenic headache (CEH) is a syndrome manifesting as chronic, unilateral headaches originating from organic or functional abnormalities in the cervical spine or its associated soft tissues (1). Epidemiological evidence suggests the prevalence of CEH ranges from 2.2 to 4.1%, with figures potentially rising to 15–20% in individuals experiencing chronic headaches (2–4). The pathogenesis of CEH is primarily linked to lesions or inflammatory irritations of the cervical structures innervated by the higher cervical nerves, leading to pain that may extend to the occipital, cervical, parietal, frontal, and periorbital areas (5, 6). The greater and third occipital nerves (GON and TON) are notably implicated in the onset of CEH, with involvement of the cervical nerve being a prevalent cause (7).

Current physical therapies for CEH include cold packs, spinal manipulation, and posture enhancement (8, 9). Nonetheless, pharmacological treatments such as nonsteroidal anti-inflammatory drugs (NSAIDs) and opioids offer only temporary relief and are associated with significant adverse effects (10, 11). Although radiofrequency ablation has effectively reduced CEH pain symptoms, it carries potential adverse effects, including sensory dullness and numbness, reported in 12–13% of cases (12, 13). This underscores the urgent need for new, safer, and more productive therapeutic options to improve the management of CEH.

Meridian sinew tuina, deriving from the Meridian Sinew theory and tuina therapy elucidated in the Emperor’s Internal Canon, is deeply rooted in traditional Chinese medical practices. Meridian Sinews (Jingjin), considered extensions of the twelve regular meridians, predominantly connect tendons, muscles, and joints. The foundational concepts of Meridian Sinew theory are detailed in the “Meridian Sinew” chapter of the Spiritual Pivot (Ling Shu) and its subsequent commentaries. This theory’s therapeutic potential for cervicogenic headache (CEH) has been explored, revealing a notable correlation between CEH and disturbances in the foot-sun meridian sinew, particularly given its extensive distribution in the head and neck area (14, 15). This distribution aligns with the regions innervated by the greater and third occipital nerves, correlating with the primary pain sites in CEH (16).

The anatomical structures associated with the foot-sun meridian sinew, ranging from superficial to deep, include the trapezius, splenius capitis, semispinalis capitis, rectus capitis posterior major, and Obliquus capitis inferior (17). Through the application of meridian sinew tuina, a manipulative therapy grounded in traditional Chinese medicine, there is potential to alleviate the compression on high cervical nerves, improve local blood circulation, reduce aseptic inflammation, and thus mitigate pain while relaxing stiff soft tissues in CEH patients (18). Clinical evidence suggests that meridian sinew tuina is a safe and effective treatment modality for CEH (19). Leveraging meridian sinew theory as a framework, Legge et al. reported favorable outcomes in managing chronic pain conditions (20).

However, the physiological mechanisms underpinning the Efficacy of meridian sinew tuina for CEH remain under-researched. Previous animal studies have shown that massage simulation can improve pain behavior in mice, an effect attributed to reduced peripheral inflammation. This reduction was mediated by the mechanosensitive channel protein Piezo and senescence-related pathways (21, 22). More recently, tuina manipulation in a neuropathic pain model was found to have an analgesic effect, potentially linked to the modulation of inflammation by noncoding RNA (23).

In 2019, the Chinese Society of Pain of the Chinese Medical Association published the clinical practice consensus titled “Clinical Diagnosis and Treatment of Cervicogenic Headache: A Consensus of Chinese Pain Specialists.” This consensus endorses the use of ultrasound-guided blocks of the greater and/or third occipital nerve (GON and/or TON) as a principal diagnostic and therapeutic approach for cervicogenic headache (CEH) (6). Traditionally, the technique for administering GON injections relied on superficial bony anatomical landmarks to infiltrate local anesthetics and corticosteroids around the nerves at the superior cervical line level. However, this approach risks inadvertently anesthetizing adjacent structures or intravascular injections into structures such as the occipital arteries due to imprecision in needle placement (24).

Ultrasound-guided techniques have revolutionized this procedure by allowing real-time visualization of the needle’s trajectory, thereby ensuring the precise delivery of an optimal dose of compounded betamethasone directly to the affected area. This method significantly reduces the localized inflammatory response, promptly relieving or eliminating pain. Additionally, ultrasound guidance provides clear visualization of the dispersion of the injected solution, reducing the likelihood of adverse effects (7, 25). Clinical evidence supports that ultrasound-guided interventions for GON and TON injections effectively alleviate CEH symptoms and improve patient quality of life (26). Given the critical nature of neck structures, this study will eschew the use of anesthetic agents to avoid the risk of severe complications.

This study introduces an innovative ultrasound localization technique for guiding meridian sinew tuina therapy in treating cervicogenic headache (CEH), followed by targeted injections into the greater and third occipital nerves. This method, devoid of radiation, offers a precision advantage over traditional body palpation and C-arm guided localization, allowing for the accurate release of the entrapped occipital nerves and adjacent soft tissues. Preliminary clinical trials have demonstrated that this integrative approach significantly alleviates pain symptoms in CEH patients.

Building on this foundation, our randomized controlled trial aims to investigate novel therapeutic strategies for CEH. We aim to assess the impact of combining ultrasound-localized meridian massage with injections into the greater and third occipital nerves. This approach will be evaluated based on its effectiveness in improving pain score indices, headache visual analog scores, pain intensity, and cervical spine mobility in CEH patients. This research seeks to contribute to developing more effective, precision-based treatments for those suffering from CEH.

## Methods and design

### Trial design

This study is designed as a single-center, randomized, parallel-controlled trial. Participants will be randomly allocated to one of two groups: the control group, which will receive ultrasound-guided injections into the greater and third occipital nerves (GON and TON), or the intervention group, which will undergo ultrasound-localized meridian sinew tuina in conjunction with GON and TON injections, maintaining a 1:1 ratio. The effectiveness of these treatments will be assessed at five distinct time points: at baseline, 3 days post-treatment commencement, 15 days post-treatment conclusion, and 30 and 60 days following the end of treatment.

This trial has been registered with the China Clinical Trial Center, bearing the identifier ChiCTR2300076128. It is committed to following the guidelines as set forth by the SPIRIT (Standard Protocol Items: Recommendations for Interventional Trials) statement (27) and adheres to the ethical standards outlined in the Declaration of Helsinki (28) (Figure 1) (see trial flow in Figure 2).

**Figure 1 fig1:**
[figure not shown]
SPIRIT schedule. This figure outlines the phases, timing, interventions, and assessments planned throughout the trial. Key abbreviations include ROM (range of motion), SF-MPQ (Short-Form McGill Pain Questionnaire), and MIT (medical infrared thermography), with ○ denoting key assessment points.

**Figure 2 fig2:**
[figure not shown]
Trial flow chart. This chart provides a visual representation of the trial’s flow, from participant enrollment to the completion of follow-up assessments.

### Participants

#### Inclusion criteria

Individuals diagnosed with cervicogenic headache (CEH) (1) as per established criteria.Participants aged between 18 and 65 years.Those willing to participate in the study and who have provided signed informed consent are also included.Individuals not currently participating in other clinical trials.Only patients with cervicogenic headache who also met a score of ≥5 on the Visual Analogue Scale for Pain (VAS) and had a duration of illness of more than 3 months will be included in the intervention and control groups.

#### Exclusion criteria

History of head, neck, or shoulder trauma or presence of infectious skin diseases.Patients with traumatic headaches, medication-overuse headaches, hypertension-related headaches, or other headache disorders.Imaging findings indicating intracranial or extracranial organic lesions, neck fractures, or dislocations.Presence of severe cardiac, cerebral, pulmonary, renal, or rheumatoid immune diseases.Long-term use of analgesics or sedative-hypnotics that cannot be discontinued for the study duration.Pregnant or breastfeeding women.

#### Suspension criteria

Occurrence or suspicion of a serious adverse event during the trial.Confirmation or suspicion of pregnancy during the treatment phase.Development of a drug allergy during treatment.

### Recruitment

Recruitment will target patients with CEH at the Tuina Department of Guilin Municipal Hospital of Traditional Chinese Medicine, Guangxi, China. Recruitment strategies include hospital-based poster displays and social media outreach, particularly through platforms like WeChat.

### Patient safety

The tuina massage will be administered with moderate force to avoid harm, strictly observing contraindications.Injections will be performed gently, ensuring slow administration of the medication to avoid entry into the vertebral artery.Aseptic techniques will be meticulously observed throughout the injection to maintain patient safety and prevent infection.

### Intervention

Before trial commencement, all participants will be thoroughly informed about the study’s potential risks and benefits. A written informed consent form will be obtained from each participant before randomization.

#### Control group: ultrasound-guided GON and TON injections

The control group will receive injections consisting of a compound betamethasone solution (1 mL of a 7 mg/1 mL concentration, produced by Hangzhou Merck Sharp & Dohme Pharmaceutical Co., Ltd.) diluted with 0.9% sodium chloride solution (4 mL of a 0.9 g/100 mL concentration). The procedural methodology for ultrasound-guided GON and TON injections adheres to the guidelines established by the Chinese Association for the Study of Pain in their “Experts Consensus on Ultrasound-guided Injections for the Treatment of Spinal Pain in China (2020 edition).” Before injection, hair in the occipital region will be trimmed.

#### Ultrasound-guided GON injection procedure

Patients are prone, with the procedure initiated on the right side for demonstration. The treatment area is first sterilized. A transverse short-axis image of the posterior occipital region is obtained using a high-frequency linear array probe (L14-6Ns, manufactured by Myeri, B-mode, operating frequency 8–12 MHz). The probe is then moved sacro-laterally until an echogenic arc shadow (the spinous process of C1 is not visible in the ultrasound image at this time) is visualized. Moving toward the sacral end reveals the first bifurcated ultrasound image (C2 spinous process). Rotating the probe counterclockwise around the C2 spinous process axis while moving laterally allows for the visualization of the C1 transverse process, resulting in a long-axis scanning image that includes the obliquus capitis inferior muscle (from the C1 transverse process to the C2 spinous process obliquely axial position). The GON is superficially identified in the obliquus capitis inferior muscle in Figure 3. A 5 mL syringe (0.53 mm × 50 mm, 25 G), inserted from the medial edge of the probe and aligned with the ultrasound plane, is used to approach the GON slowly. Upon confirming needle placement via negative aspiration, 2.5 mL of the medication is administered. Following injection, the puncture site is covered with a sterile dressing and localized pressure is applied for 3 min.

**Figure 3 fig3:**
[figure not shown]
Ultrasound-guided GON scan. **(A)** This illustration illustrates the probe positioning for greater occipital nerve (GON) scanning along the C1 transverse process to the C2 spinous process oblique axis. **(B)** The ultrasonographic image depicts the anatomical relationship between the greater occipital nerve and surrounding structures. Abbreviations include C1 (atlas C1), C2 (axis C2), GON, C1 transverse process (C1 TP), semispinalis capitis muscle (SSCM), obliquus capitis inferior muscle (OCIM), C2 dorsal root ganglion (C2 DRG), and the trapezius muscle. The blue rectangle (A) indicates the probe position.

#### Ultrasound-guided third occipital nerve (TON) injection procedure

Participants are positioned prone to this procedure. The procedure begins by placing the cephalad side of the probe over the mastoid process, aligning it parallel to the cervical spine’s long axis. As the ultrasound probe glides sacralward, the transverse processes of C1 and C2 become visible on the ultrasound display. Continuing the movement sacralward and slightly towards the spinous process, a wave-like acoustic shadow emerges, depicting the articulations between C2-C3 and C3-C4, as illustrated in Figure 4. At this juncture, the TON, traversing over the C2-C3 joint surface, is identified. A 5 mL syringe (0.53 mm × 50 mm, 25 G) is inserted from the probe’s lateral sacral edge with the probe stabilized. The needle is guided in-plane towards the TON, and upon confirming the position via negative aspiration, 2.5 mL of the therapeutic solution is administered. Following injection, the site is covered with a sterile dressing and compressed locally for 3 min to ensure hemostasis.

**Figure 4 fig4:**
[figure not shown]
Ultrasound-guided Third Occipital Nerve (TON) scan. **(A)** The probe is placed for the long-axis scan of the C2-C3 articular pillar, illustrating the path of the third occipital nerve. **(B)** Ultrasonographic visualization of the third occipital nerve, highlighting its anatomical relationship with surrounding structures. C2-C3 facet joint (C2-C3), C3-C4 facet joint (C3-C4), C4 vertebra (C4), Midline (×), Probe indication (Blue rectangle B).

### Intervention group: ultrasound localized meridian sinew tuina combined with GON and TON injections

#### Treatment protocol

The intervention entails a regimen of daily meridian sinew tuina therapy for three consecutive days, with each session spanning 30 min, starting from the baseline. On the third day, participants receive a single session of ultrasound-guided injections into the greater and third occipital nerves (GON and TON), marking the completion of the treatment course. Each participant undergoes one full course of this combined treatment.

#### Meridian sinew tuina

Certified tuina therapists with at least three years of clinical experience in traditional Chinese medicine perform all treatments. These practitioners have undergone rigorous training and assessments in tuina techniques, particularly for this study. Initially, therapists utilize ultrasound to precisely locate the GON and TON on the right side. They then outline the treatment areas “A” and “B” adjacent to the ultrasound probe with a marker, as shown in Figures 3A, 4A. The participant, positioned prone, undergoes specific tuina techniques, including Dhyana-thumb-pushing (Yi Zhi Chan pushing), plucking, kneading with the Thumb, and Thumb pressing in areas “A” and “B” for 20 min, as demonstrated in Figure 5.

**Figure 5 fig5:**
[figure not shown]
Meridian sinew tuina techniques. **(A)** Dhyana-thumb-pushing (Yi Zhi Chan pushing). **(B)** Plucking. **(C)** Kneading with the Thumb. **(D)** Thumb pressing.

Subsequently, the therapist employs palpation to assess the head and neck regions, mapping the superficial to deep layers along the foot’s solar meridian tendons. The examination progresses from gentle to firm pressure, utilizing techniques such as following, pressing, and touching to identify subcutaneous areas of tenderness or nodules. Targeted tuina maneuvers like thumb kneading, Thumb pressing, and lateral plucking are applied to these points, especially along the foot’s solar meridian tendons in the head and neck region. This process also aims to relax muscles such as the trapezius, splenius capitis, semispinalis capitis, rectus capitis posterior major, and Obliquus capitis inferior. The total treatment time for this phase is 10 min.

### Observational indicators

#### Primary observational indicators

##### Short-Form McGill Pain Questionnaire (SF-MPQ)

Pain evaluation is performed using the SF-MPQ, a globally recognized instrument for describing and quantifying pain experiences (29). The SF-MPQ consists of three main components: the Pain Rating Index, which assesses the quality of pain; the Visual Analogue Scale for headache, offering a subjective measure of pain intensity; and the Present Pain Intensity section, which provides a snapshot of the current pain level.

#### Secondary observational indicators

##### Cervical Range of Motion (ROM)

As the American Academy of Orthopedic Surgeons recommended, ROM evaluation is an essential method for quantifying mobility within the cervical joint (30). This measurement involves assessing the extent of movement in various directions from a standardized neutral position, noted as 0°. The established normal ranges of motion are as follows: for flexion and extension, from 0° to 45°; for lateral flexion (both left and right), from 0° to 40°; and for rotation (left and right), from 0° to 70°.

##### Medical infrared thermography

*Instrumentation*: The study employs the X640D digital infrared thermography system by Ge Wu You Xin Company. Image analysis is conducted using IRToolPRo software, which provides a comprehensive temperature detection range from 0°C to 300°C with a precision of ±0.3°C. The system boasts a pixel size of 17UM, a frame rate 30 Hz, and operates within the 8 ~ 14UM band. For enhanced visual contrast, the color scale mode is selected.*Testing conditions*: The testing environment is precisely controlled to ensure optimal data accuracy. The laboratory temperature is maintained between 20°C and 23°C, with strict avoidance of any direct sunlight or artificial light exposure and minimal indoor air movement (31). Relative humidity is regulated within the 20 to 30% range, creating ideal conditions for thermographic analysis.*Operational method*: Participants first acclimate to the laboratory environment by resting quietly for five minutes, allowing skin temperature stabilization. They then stand upright, exposing the head and neck area, and position themselves one meter from the infrared thermography camera. The attending physician adjusts the camera focus to ensure the capture of clear thermal images. Infrared thermal data collection encompasses the highest, lowest, and average temperatures at the skin surface areas corresponding to the bilateral greater occipital nerve and the third occipital nerve, as illustrated in Figure 6.

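### Thermography: the head and neck are exposed only after the five-minute stabilisation rest, and no time from exposure to image is set, so skin covered until then gets no equilibration period

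*Protocol article*

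**What the plan says.** The Operational method paragraph of the Medical infrared thermography section gives the steps in sequence:

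1. Participants start by "resting quietly for five minutes, allowing skin temperature stabilization. They then stand upright, exposing the head and neck area".
2. They place themselves one metre from the camera.
3. "The attending physician adjusts the camera focus to ensure the capture of clear thermal images".

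The data taken are the "highest, lowest, and average temperatures at the skin surface areas corresponding to the bilateral greater occipital nerve and the third occipital nerve". The Testing conditions paragraph controls the room: "The laboratory temperature is maintained between 20°C and 23°C", with limits on light, air movement and humidity. The Instrumentation paragraph gives a "temperature detection range from 0°C to 300°C with a precision of ±0.3°C".

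The article does not say that collar or hair is cleared before or during the rest. It gives no wait after exposure and no fixed time from exposure to capture.

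On use, the Abstract's methods describe thermography as a secondary outcome that measures skin temperature change from before to after the intervention. Its discussion states that "MIT is utilized to provide objective evidence of the efficacy of CEH". The Data analysis section plans Pearson correlations of the thermography difference with the other outcome measures.

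**The concern.** The rest exists to let skin temperature settle. In the written order, exposure is a step that follows it, so skin uncovered at that step has not been resting bare in the room. It starts to cool when it is uncovered, and the image is taken after whatever time standing, positioning and focusing happen to need. The reading then depends partly on what the patient wore, how the hair lay and how long the set-up took, and all of these can vary from visit to visit.

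The outcome is an absolute temperature used as a change, so the error of both images enters each change score. Random error in the change score pulls its correlations with the other outcomes towards zero, in a trial of 30 patients per group. At stake is the precision of an outcome that the article presents as objective evidence.

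**Working it through.** **Step 1: order of the steps.** The purpose of stabilising the skin is attached to the rest, which comes first. Exposure is attached to standing up, which comes after. Positioning and focusing follow, with no stated duration. For skin already bare during the rest, the rest does its job. For skin uncovered on standing, the equilibration period is only the unspecified set-up time.

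**Step 2: is there a figure in the plan to reproduce?** No. The article gives no cooling rate, no expected temperature change and no standard deviation for thermography. The only benchmark is the instrument precision of ±0.3°C.

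**Step 3: illustration on assumed inputs.** Let D be the total fall in temperature of newly uncovered skin and tau its time constant. With exponential cooling, the excess remaining t minutes after exposure is D × exp(−t/tau). Two images taken at t1 and t2 therefore differ by

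D × [exp(−t1/tau) − exp(−t2/tau)].

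Assumptions, none from the documents: D = 0.5 to 3°C; tau = 3 to 10 min; t1 = 0.5 min at one visit and t2 = 3 min at another, a timing difference of 2.5 min.

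| D (°C) | tau = 3 min | tau = 5 min | tau = 10 min |
|---|---|---|---|
| 0.5 | 0.24 | 0.18 | 0.11 |
| 1 | 0.48 | 0.36 | 0.21 |
| 2 | 0.96 | 0.71 | 0.42 |
| 3 | 1.44 | 1.07 | 0.63 |

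Worked cell, D = 1 and tau = 5: exp(−0.1) − exp(−0.6) = 0.905 − 0.549 = 0.36°C.

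The range is about 0.1 to 1.4°C. At D = 0.5°C every cell lies below 0.3°C. At D = 1°C two of three cells exceed it, and at 2°C or more all do. At D = 0 (area already bare and settled) the difference is zero.

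**Step 4: the same timing difference if exposure comes before the existing rest.** The images then fall at 5.5 and 8 min after exposure, and each cell is multiplied by exp(−5/tau): 0.19 for tau = 3, 0.37 for tau = 5, 0.61 for tau = 10. The table's range becomes about 0.05°C (D = 0.5, tau = 3) to 0.39°C (D = 3, tau = 5). Reordering alone reduces the timing effect but does not remove it. Fixing the time from exposure to capture addresses the remainder, because t1 and t2 are then equal.

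**Step 5: direction.** The same procedure is described for both arms, and nothing in the article ties capture timing to arm. The expected effect is added variance, not a shift in the group comparison.

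**The case against.** The strongest reply is that coverage during the rest is inferred. The article does not say that the neck is covered, and exposing the area may only describe how the patient presents it to the camera. This stands in part. A reader might infer that the measured skin is never equilibrated; the documents do not support that, because some or all of it may be bare throughout. What remains is conditional: skin covered until the patient stands gets no settling period.

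A second reply is that collars, hair and capture timing are operating details that a journal article leaves to the full protocol. That would be fair for a mere omission. Here the article states a sequence, in a section that specifies room climate, camera distance and rest length, and the sequence works against the purpose it gives for the rest.

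Third, the magnitudes rest on assumptions, and the top of the range needs the largest fall together with the fastest cooling. This stands. The ±0.3°C is also an instrument figure and not an effect size, so the documents cannot show that timing would create or conceal a treatment effect.

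Fourth, a reader might infer between-group bias, or that five minutes is too short. Neither is supported. No link between timing and arm is described, and the article contains no standard for judging the length of the rest. Nor does the text establish that thermography is done at all five assessments: the Abstract speaks of before and after the intervention, and the schedule figure is not available.

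**Conclusion.** The point holds as a limited measurement issue. The written order gives no equilibration period to skin uncovered after the rest, and nothing fixes the time to capture. The consequence is avoidable noise in the thermography changes and attenuated correlations with the other outcomes. It is mainly non-differential and does not touch the SF-MPQ analysis.

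The size cannot be derived from the documents. The illustrative 0.1 to 1.4°C depends on the assumed fall, time constant and 2.5-minute timing difference. It is near zero if the area is already bare, and stays within the stated precision if the fall is only 0.5°C. The case for acting rests on the stated sequence and the very low cost of correcting it, not on a demonstrated loss.

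**What to change.** Reorder the Operational method: clear collar and hair and expose the head and neck area first, then take the existing five-minute rest with the area bare, then stand, position and focus. Capture the image at a fixed time after exposure and record that time on the case report form. Apply this identically in both arms and at every visit where thermography is done.

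The cost is one reworded sentence and one recorded time. No extra visit time is needed because the existing rest is used. A longer rest is optional and is not part of this point.
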